### Study objectives and hypotheses

The first objective of this study is to investigate the effects of ATD as a physiologically induced short-term central nervous serotonergic deficit on mood in adolescents with MDD (Phase A of the study) prior to open label treatment initiation with SSRI fluoxetine (Phase B of the study). We expect that, in Phase A, ATD will have dysfunctional effects on mood, emotional face recognition, aspects of reversal learning, and attention-related cognitive parameters as assessed within a testing battery, when compared to a balanced control condition. Such results would reflect a 5-HT sensitivity to ATD with regards to the aforementioned parameters relevant for depression [16, 17], and would be in line with the findings amongst the adult population [10, 18–20].

The second objective of this study is to determine if the effects of ATD on mood as a physiological 5-HT-related neurochemical and dietary challenge procedure predicts treatment response to SSRI administration after a period of 12 weeks of open label pharmacological treatment with fluoxetine (Phase B). We hypothesise that the effects of ATD administration on mood from Phase A will predict clinical improvement relating to depressive symptoms and overall depressive symptomatology 12 weeks into SSRI treatment (Phase B). Specifically, we hypothesise that ATD may be indicative of serotonergic vulnerability in relation to symptoms relevant for adolescent depression.

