### Subjects and eligibility criteria

This pilot study aims to recruit *N* = 20 participants, and all participants who are referred to the study will be screened. Inclusion criteria for this study are as follows: adolescents aged between 12 and 17 years with a confirmed diagnosis of MDD (ICD-10 or DSM-5; diagnosis to be confirmed through the administration of the Kiddie Schedule for Affective Disorders and Schizophrenia (K-SADS) [21], as well as a full psychiatric assessment), no current suicidal ideation or suicidal plans, no other psychiatric co-medications at study entry, IQ > 85 (screened through the use of the Wechsler Abbreviated Scale of Intelligence (WASI-II) [22]), and no active or past eating disorder. Exclusion criteria include current abuse of alcohol and use of illicit substances, pregnancy in female participants, chronic medical or neurological disorders, subjects whose primary language is not English, treatment with other histaminergic or dopaminergic medications, disorders of amino acid metabolism, and contraindications against the use of fluoxetine. Participation in this study is entirely voluntary. Once recruited, participants will be able to withdraw their consent at any time by informing the study team.

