#### Phase B

Phase B will commence between 24 and up to a maximum of 72 h after the second day of Phase A. Phase B will consist of a 12-week open label pharmacological treatment as usual with the SSRI fluoxetine. Participants will be required to attend weekly follow-up sessions with the study doctors. Fluoxetine will be prescribed and administered in a fixed-dose approach, in accordance to the NICE Clinical Guidelines – Treatment of Depression in Children and Young People [33]. Specifically, the administration of fluoxetine will start at 10 mg daily and will be increased to 20 mg daily after 1 week.

During this second phase (Phase B), participants are free to participate in other treatments such as psychological treatment or psychotherapy (e.g. cognitive behavioural therapy) if medically indicated, and will not be excluded from the study unless the treatment with fluoxetine is stopped. However, these additional treatments will be taken into consideration with the statistical analysis and may lead to post-hoc exclusion of some participants. Under this approach, the data obtained will largely reflect the clinical reality in the sample served.

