##### Biochemical assessments and psychological and cognitive tasks to be conducted in Phase B

Blood, mood and cognitive measurements will also be taken in Phase B. During Phase B, blood samples will be taken. The purpose of the blood testing during Phase B is to monitor fluoxetine availability throughout the course of the study. Fluoxetine levels assessed during this phase will also allow the calculation of preliminary dose–response relationships regarding the suggested predictors of treatment response. Compliance with the fluoxetine treatment will also be monitored through an empty packet return and verbal report. Blood samples will undergo basic laboratory processing before storage in an electronically lockable freezer at –80 °C degrees, before analysis. Participants’ mood will be measured on a weekly basis, using the BDI, HDRS, CDRS-R and POMS. Additionally, the Child Behaviour Checklist will be administered during the 6- and 12-week follow-up of Phase B to assess psychopathology. The cognitive tasks that were completed during each study day of Phase A will also be completed at the 12-week follow-up of Phase B. These tasks include the TAP, the Facial Expression Recognition Task and the Reversal Learning Task.

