#### Data preparation and statistical analysis

The data that will be collected will consist of information relating to medical history, mood, scores on cognitive tasks and blood samples. All data, including blood samples will be de-identified. Codes for the depletion (ATD) and sham depletion (BAL) will be held in an envelope in a securely locked space in the unlikely event of an emergency that requires the code to be broken. Only researchers on the listed research team will have access to the final dataset.

To examine changes in response to ATD (mood, cognitive parameters and tasks, amino acid concentrations, etc.) as well as after treatment (mood symptoms, cognition, SSRI monitoring) a series of repeated measures ANOVAs will be conducted with time (baseline, ATD administration and 12 weeks into treatment) and challenge procedure (ATD/BAL administration) as within-subject factors. We will also evaluate for a significant effect of relevant baseline amino acid levels on the observed changes. If such a significant interaction is discovered, ANCOVAs will be performed with baseline values as covariates.

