#### Power analysis

As this study is being conducted within a cohort of adolescents, we expect there to be possibly smaller effects [34], which could be due to reduced neurochemical effects, as well as difficulties with subjective mood ratings by the participants. For *N* = 20 participants, a power of 0.97 was calculated (ANOVA, effect for within-subjects factors) to detect small effects (effect sizes of 0.4) with a significance level of α = 0.05 (two-tailed testing, critical F = 3.26). This is in line with previous research showing that mood effects observed after ATD can be rather small in healthy subjects, but possibly more severe in patients affected or vulnerable to depression [35, 36]. Power calculations were performed with G*Power Software, Version 3.1.3 [37]. It is important to note, however, that these calculations are preliminary (conducted before study initiation) and are currently an estimate. The data of this study can be used to inform future larger scale studies. Individuals who are drop-outs or lost to follow-up will be replaced to meet the power calculations.

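### Phase B scales are collected weekly, but the stated ANOVA uses only week 12 and drop-outs are replaced, so the results describe completers and weeks 1 to 11 enter no stated analysis

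*Protocol article*

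**What the plan says.** The Phase B section of the protocol article sets the follow-up: "Phase B will consist of a 12-week open label pharmacological treatment as usual with the SSRI fluoxetine", with weekly visits. The Phase B assessment section states that participants' "mood will be measured on a weekly basis, using the BDI, HDRS, CDRS-R and POMS".

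The section on data preparation and statistical analysis covers both the response to the challenge and the changes after treatment. For both, "a series of repeated measures ANOVAs will be conducted" "with time (baseline, ATD administration and 12 weeks into treatment") and challenge procedure as within-subject factors. ANCOVAs follow if baseline amino acid levels matter. No analysis of weeks 1 to 11 is described.

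The objectives place the response hypothesis "12 weeks into SSRI treatment (Phase B"). On losses, the Power analysis section says: "Individuals who are drop-outs or lost to follow-up will be replaced to meet the power calculations". The Recruitment section also provides for replacing participants who discontinue. Neither section says whether the scores already collected from those participants are analysed. The sample size is fixed as follows: "This pilot study aims to recruit *N* = 20 participants".

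**The concern.** The second objective asks whether the mood effect of ATD predicts response to fluoxetine. With 20 people, that depends on how well each person's response is measured and on whose response is measured at all.

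Two features of the stated plan bear on this. First, the scores from weeks 1 to 11 do not inform the week-12 result. Second, a person who stops at week 8 would have about eight weekly scores per scale and contribute none of them to the Phase B comparison. The replacement brings the count back to 20 but is a different person who stayed. The Phase B sample is thereby selected on completion. If completion is related to response, both the response estimate and its association with the ATD effect can be biased.

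The article names both the method and the time levels, so this is a stated choice and not a detail left to a fuller document.

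**Working it through.** **The plan's own figure.** The Power analysis section states that "a power of 0.97 was calculated (ANOVA, effect for within-subjects factors"), for N = 20, effect size f = 0.4, α = 0.05 and critical F = 3.26. The number of measurements m, the number of groups g and the correlation ρ are not stated. I assumed m = 3, g = 2, ρ = 0.5 and ε = 1.

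- λ = f²·N·m/(1 − ρ) = 0.16 × 20 × 3/0.5 = 19.2
- df = (m − 1) and (N − g)(m − 1) = 2 and 36
- critical F = 3.259, power = 0.972

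Both stated figures reproduce. With m = 2 the critical F is 4.38 to 4.41 and with m = 4 it is 2.77 to 2.78, so neither fits. The power calculation is therefore consistent with a three-level time factor that has a single Phase B level.

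**Share of Phase B data used.** One of about 12 weekly assessments per scale, 1/12 = 8%.

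**If losses were not replaced.** With the same inputs and n people having week 12:

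| Loss | n | λ | Power |
|---|---|---|---|
| 0% | 20 | 19.20 | 0.972 |
| 10% | 18 | 17.28 | 0.953 |
| 20% | 16 | 15.36 | 0.924 |
| 30% | 14 | 13.44 | 0.878 |
| 40% | 12 | 11.52 | 0.810 |

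The loss rates are assumptions; the article gives none. Replacement would restore the nominal power, so what remains is selection.

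**Precision of individual response (illustration).** Assume a linear course, scores at weeks 0 to 12 (13 points), true 12-week change with SD 1, single-visit error with SD 1, and lag-1 error autocorrelation φ. Reliability = 1/(1 + error variance of the estimated change). The apparent correlation is 0.60 × √reliability, for a true correlation of 0.60.

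- Endpoint difference: error variance = 2(1 − φ¹²). At φ = 0 this is 2, so reliability = 1/3 = 0.333 and the apparent correlation is 0.346.
- Least-squares slope × 12: at φ = 0 the error variance is 144/182 = 0.791, where 182 is the sum of squared deviations of weeks 0 to 12. Reliability = 1/1.791 = 0.558 and the apparent correlation is 0.448.

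| φ | Endpoint: reliability, apparent r | Weekly slope: reliability, apparent r |
|---|---|---|
| 0 | 0.333, 0.346 | 0.558, 0.448 |
| 0.3 | 0.333, 0.346 | 0.445, 0.400 |
| 0.5 | 0.333, 0.346 | 0.373, 0.367 |
| 0.7 | 0.336, 0.348 | 0.321, 0.340 |

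An optimally weighted (generalised least squares) slope does a little better at high autocorrelation: apparent r of 0.375 at φ = 0.5 and 0.356 at φ = 0.7.

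A check on the variance of the estimated change gives the same picture. The endpoint difference has 2.53 times the variance of a linear trend on all 13 points under compound symmetry, but only 1.00 to 1.07 times under a first-order autoregressive pattern with ρ from 0.7 to 0.95. The article gives no correlation pattern.

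**The case against.** **Week 12 is the pre-stated target.** This stands: analysing the hypothesised time point is legitimate. Weekly visits also serve safety review, so weekly collection alone does not oblige a weekly efficacy analysis. A reader might infer that the endpoint itself is wrong; the article does not support that. The point is only that the week-12 estimate ignores the observed weeks of people who never reach it.

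**The precision figures concern an analysis the article does not describe.** This stands. The stated ANOVA compares mean scores over time and challenge; it computes no correlation between individual ATD effect and individual response. The figures illustrate how well response is measured for the second objective, not a loss in the ANOVA. A reader who stops at low autocorrelation might infer a firm gain, to 0.40 to 0.45. At autocorrelation 0.5 to 0.7 that gain almost or entirely disappears.

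**Baseline may be more than one score.** BDI, HDRS and CDRS-R are taken at the start of both Phase A days, and the article does not say how baseline is formed. Averaging two scores with independent errors would cut the endpoint error variance to 1 + 1/2 = 1.5 and raise its reliability to 1/2.5 = 0.40, which narrows the gap further.

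**Response may look too favourable.** A reader might infer that the completer analysis overstates response because poor responders leave. That is plausible, but the article gives no dropout rate and no information on who leaves, and the Phase B objective is prediction rather than an estimate of response level. Neither direction nor size can be asserted.

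**A straight-line model would be a poor replacement.** This stands. The Abstract and Background describe delayed response and varied onset, so a linear random slope could misstate week-12 change. The remedy needs a flexible time form.

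**It is a condensed account of a pilot.** A fuller plan may add weekly models. But the article does fix the time levels, and those can be judged as written.

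**Conclusion.** The point holds in a limited form. Weekly scores are collected, the stated ANOVA has one Phase B time level, and drop-outs are replaced with no statement that their data are used. As written, weeks 1 to 11 enter no stated analysis and the Phase B results describe completers. That last step rests on the usual requirement of classical repeated measures ANOVA for complete data, which the article does not spell out.

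The main consequence is possible selection bias in response and in its relation to the ATD effect, of unknown size and direction. The gain in precision is secondary and ranges from none to moderate, under a linear course with true-change SD equal to error SD and error autocorrelation from 0.7 down to 0. The change is worth making because it is cheap, not because a large loss has been shown.

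**What to change.** Keep week 12 as the target and amend the analysis text for the Phase B scales:

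- Use a mixed model for repeated measures on all weekly scores, with week as categorical or in another flexible form and the pre-treatment score as covariate. State how that score is formed.
- Use a parsimonious within-person covariance. An unstructured matrix for 12 visits has 12 × 13/2 = 78 parameters, too many for 20 people.
- Report the week-12 contrast from the model, and the ATD-effect-by-time term evaluated at week 12.
- Include all observed weeks of participants who discontinue, alongside their replacements.
- Keep the week-12 completer ANOVA as a sensitivity analysis.

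The cost is revised wording and somewhat more analysis work; no visits, data or participants are added. There are downsides. A time form and covariance must be chosen in advance, and the model relies on data being missing at random, so it reduces dropout bias without guaranteeing its removal. With fully categorical time and complete data, the week-12 contrast is essentially the endpoint comparison. The benefit then lies in keeping those who stop early, and any gain in precision has to come from a smoother time form.

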### Trial design

In Phase A, this study will use a randomised, double-blind, within subject repeated measures design. During this phase, participants will undertake the challenge procedures (either ATD or balanced control condition (BAL)) on two separate study days, spaced at a maximum of 7 days apart. In Phase B, this study will employ an open label fluoxetine treatment for a period of 12 weeks.

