### Intervention

This study will consist of one baseline session and two study phases, Phase A and Phase B. The timing of the assessments and study phases that will be conducted is illustrated in Fig. 1.

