##### Biochemical assessments and psychological and cognitive tasks to be conducted in Phase A

Several assessments and cognitive tasks will be conducted in Phase A, as outlined in Fig. 1. Assessments include the sampling of blood, mood assessments and cognitive testing.

The primary purpose of the blood samples collected at the beginning of Phase A is to assess baseline levels of TRP and other amino acids. The blood samples that will be collected during the two study days will allow measurement of the relevant amino acids contributing to the depletion. At the beginning of each study day in Phase A, participants will be required to complete the Beck Depression Inventory II (BDI-II) [25], the Hamilton Depression Rating Scale (HDRS) [26] and the Children’s Depression Rating Scale – Revised (CDRS-R) [27]. On the first study day, parents or caregivers will also complete the Child Behaviour Checklist [28]. Mood will be monitored on the two study days through the use of the Profile of Mood States (POMS) after ATD or BAL administration, in 30-min time intervals [29].

Cognitive assessments that will be conducted in Phase A include the Tests for Attentional Performance (TAP, PSYTEST, Herzogenrath, Germany) [30]. The TAP subtests that will be used include Alertness, Working Memory, Divided Attention and Sustained Attention. Between each test there will be a break of approximately 10 min. The Facial Expression Recognition Task will also be conducted on each study day of Phase A [31], as well as a Reversal Learning Task [32].

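### The time-by-challenge within-subject ANOVA cannot be fitted as stated, because week 12 (and the single baseline session) has no ATD or BAL level

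*Protocol article*

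**What the plan says.** The section on data preparation and statistical analysis covers both the response to ATD and the change after treatment in one sentence: "as well as after treatment (mood symptoms, cognition, SSRI monitoring) a series of repeated measures ANOVAs will be conducted". It then gives the factors and their levels: "time (baseline, ATD administration and 12 weeks into treatment) and challenge procedure (ATD/BAL administration) as within-subject factors".

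The design is described elsewhere in the Protocol article:

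- **Challenge (Trial design).** In Phase A "participants will undertake the challenge procedures (either ATD or balanced control condition (BAL)) on two separate study days".
- **Baseline (Intervention).** "This study will consist of one baseline session and two study phases, Phase A and Phase B".
- **Treatment (Trial design).** "In Phase B, this study will employ an open label fluoxetine treatment for a period of 12 weeks".
- **Study-day depression scales (Phase A assessments).** "At the beginning of each study day in Phase A, participants will be required to complete the Beck Depression Inventory II (BDI-II"; the same sentence adds the HDRS and the CDRS-R.
- **Study-day mood (Phase A assessments).** Mood is monitored "through the use of the Profile of Mood States (POMS) after ATD or BAL administration, in 30-min time intervals".
- **Phase B mood (Phase B assessments).** "Participants’ mood will be measured on a weekly basis, using the BDI, HDRS, CDRS-R and POMS". The cognitive tasks are repeated once, at week 12.

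**The concern.** Two crossed within-subject factors require every participant to be observed at each combination of their levels. Here one factor, the challenge, exists only on two days before treatment starts, while the other runs on to the end of treatment. The stated layout therefore asks for an ATD value and a BAL value at week 12, when no challenge is given. One time level is also named after ATD, which is itself a level of the other factor. Read literally, the combination of that time level with BAL contradicts itself.

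This is the only model the article states for the first objective (ATD versus BAL) and for the change on fluoxetine. If it cannot be run as written, the analyst must decide how to fill or drop cells, possibly after seeing the data from 20 participants. Different choices give different estimates and different error rates.

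**Working it through.** **The plan's own figure.** The Power analysis section states power 0.97 for N = 20, effect size 0.4, α = 0.05 and critical F = 3.26. It does not give the number of groups k, the number of measurements m, the correlation ρ or the sphericity factor, so these are assumptions here. For a within-subjects effect with sphericity:

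- df1 = m − 1, df2 = (N − k)(m − 1), λ = f²·N·m/(1 − ρ).
- With k = 2, m = 3, ρ = 0.5: df = (2, 36), λ = 0.16 × 20 × 3/0.5 = 19.2, critical F = 3.259, power = 0.972. Both stated figures are reproduced.
- With k = 1 and the rest unchanged: df = (2, 38), critical F = 3.245, power = 0.972. The critical value does not match.

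The figure thus fits one three-level within factor with two groups. It does not describe two crossed within factors, so it does not show how the stated model was meant to be filled.

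**Cells available per participant.** A 3 × 2 factorial has 1 + 2 + 1 + 2 = 6 parameters (intercept, time, challenge, interaction).

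| Reading | Baseline | Challenge | Week 12 | Distinct cells | Rank of design |
|---|---|---|---|---|---|
| Complete layout | 2 | 2 | 2 | 6 | 6 |
| One baseline session | 1 | 2 | 1 | 4 | 4 |
| Start-of-day scales as baseline | 2 | 2 | 1 | 5 | 5 |
| Start-of-day baseline, middle level taken literally as ATD only | 2 | 1 | 1 | 4 | 4 |

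Three parameters involve the challenge (one main effect, two interaction terms). With four cells on the one-session reading, only one challenge contrast can be estimated: ATD minus BAL at the challenge itself. With five cells, two can. No available reading supports all three.

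**Illustration: copying single values into both challenge levels.** The article does not propose this; it is assumed here to show what an improvised repair could do. Each participant's ATD-BAL differences across the three times become (0, dᵢ, 0). Let d̄ and s be the mean and SD of dᵢ, n = 20, and t = d̄/(s/√n), the ordinary paired t.

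- *Challenge main effect.* The estimate is d̄/3 and its standard error is (s/√n)/3, so the test statistic is still t. The coefficient is one third of the ATD-BAL difference and the test is unchanged.
- *Interaction.* Numerator mean square: n·d̄²(1/9 + 4/9 + 1/9)/2 = n·d̄²/3. Error mean square: (2/3)(n − 1)s²/[2(n − 1)] = s²/3. Hence F = n·d̄²/s² = t², which truly follows F(1, 19). Uncorrected, it is compared with the 5% point of F(2, 38), 3.245, instead of that of F(1, 19), 4.381. P(F(1, 19) > 3.245) = 0.0875. A simulation of 20,000 null trials gave 0.086, against 0.050 for the paired t.
- *With a Greenhouse-Geisser correction.* The differences vary in one direction only, so epsilon = 1/2, the reference becomes F(1, 19), and the test is the paired t-test again.
- *Start-of-day baselines, only week 12 copied.* Simulated uncorrected error was 5.1% to 5.9%, for assumed correlations of 0 to 0.5 between the two ATD-BAL differences.

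**The case against.** The best defence is that the sentence is compressed. It speaks of a series of ANOVAs over mood, cognition, amino acids and drug monitoring. Fluoxetine levels cannot have an ATD/BAL factor, so the sentence may list factors for a family of models, with details in a full protocol or analysis plan not shown here. The time level named after ATD may simply mean administration of the challenge. The Mood part of Expected outcomes compares ATD-induced change with both baseline and BAL, so the BAL day is plainly meant to be used. The start-of-day BDI-II, HDRS and CDRS-R, and possibly the first blood sample, can be labelled by study day.

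Much of this stands, and it limits the point. A reader might infer four stronger things that the article does not support:

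- *That baseline can never carry a challenge label.* For the start-of-day scales it can. Study-day POMS is described only after the drink.
- *That the BAL day is left out.* Loose wording is the likelier explanation.
- *That the within-day POMS ratings or the weekly ratings before week 12 are discarded.* The section does not say how they enter.
- *That the trial's test has an 8.8% error rate, or that the ATD-BAL test is spoiled.* That rate needs both a copying step the article never mentions and no sphericity correction, on which it is silent. The main-effect test is unaffected even then.

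The defence does not fill the week-12 cells. The article did not leave the model open: it attached both factors and all three time levels to the whole series. That stated structure conflicts with the design under every reading.

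**Conclusion.** The stated analysis does not fit the design. Four of the six required cells exist with the single baseline session, and five on the most generous reading, so the time-by-challenge model cannot be fitted as written. This rests only on the article's account of when the challenge is given and on week 12 being one assessment on fluoxetine.

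The one-third coefficient and the 8.8% rejection rate are illustrations of one possible improvised repair, not properties of the plan. The underlying questions remain answerable from the planned data. The fault lies in the model statement, and it should be corrected before the data are analysed.

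**What to change.** Replace the sentence with two analyses.

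1. **Phase A.** A within-participant comparison of ATD with BAL for post-drink mood, cognitive scores and amino acids. Include condition and study day (period) and, where an outcome is measured repeatedly within the day, time since the drink and condition × time. Report the ATD-BAL difference with its confidence interval.
2. **Phase B.** A repeated-measures analysis over time only, from pre-fluoxetine to week 12, with no challenge factor. Name the assessment that serves as the pre-fluoxetine value for each outcome.

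Two ANOVAs on these lines would cure the error. A mixed model using all weekly ratings is a reasonable option for Phase B but is not required. If an ANOVA with more than two time levels is kept, state the sphericity correction.

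The cost is a change of wording and slightly more analysis work. No new data, visits or participants are needed.
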